### Interventions

2.8

#### The intervention group

2.8.1

Participants allocated to the IG will engage in a 12‐week PA programme comprising aerobic exercise and resistance training, in addition to their usual diabetes care. The exercise goal will be at least 120 min/week of exercise distributed over at least 3 days/week. In total, participants in the IG will be asked to engage in 36 sessions of exercise over the 12‐week period, with each session lasting between 35 and 45 min. Of the 36 exercise sessions, 14 individualised sessions will be conducted at the physiotherapy department of the Korle‐Bu Teaching Hospital. The remaining 22 exercise sessions will be self‐delivered at home. Each exercise session will be structured as follows:
3 min of warm‐up (stretching exercises);10 min of resistance exercise (exercises targeting upper and lower large body muscles using TheraBand). The specific resistance exercise prescribed in this program will be: chest press, shoulder curls targeting the upper body muscles, and leg press targeting lower body muscles;20–30 min of aerobic exercise (walking) at moderate pace (4.5–5.1 km/h = 3.5 MET) or brisk pace (5.2–5.6 km/h = 4.3 MET) (Ainsworth et al., 2011); and2 min of cool‐down (stretching exercises).

##### Baseline visit and exercise demonstration

The programme comprises a 45‐min education session that will include content relating to the importance of PA, including recommended PA targets, and the PA intervention (e.g., type, intensity, duration and frequency). The education session will be organised during the participants' baseline visit to the NDMRC and will be led by a nurse and a physical therapist (PT). The education session will teach participants about self‐regulation in relation to the PA programme. Self‐regulation, as explained by social cognitive theory, relates to the ability of the individual to set realistic goals to achieve certain behaviours (Bandura, 1989). Participants will also be advised about prevention of injury (safety issues), overcoming challenges, and sources of social support.

##### Week‐1

In Week‐1, all three training sessions will be done at the physiotherapy department of the Korle‐Bu Teaching Hospital under the supervision of a PT. The reason for the supervised exercise session is to ensure that participants can perform each type of exercise correctly and within the recommended safety standards. At the start of week 1, participants will be assessed to confirm that they are well enough to participate. Each participant will be assessed by the PT for the following measures: (a) FBG, (b) BP and (c) HR. Target HR will be based on the recommended safe range of 64%–76% of maximum heart rate, which is determined by subtracting the participant's age from 220 (Physical Activity Guidelines Advisory Committee, 2009; Riebe et al., 2018). Exercise in week 1 will be limited to 35 min (20 min of walking and 10 min of resistance training plus 5 min of warm‐up and cool‐down) targeting 50%–60% of maximum heart rate.

To prevent the incidence of hypoglycaemia, participants will be advised, during the education session, on the common symptoms of hypoglycaemia, such as abnormal sweating, shakiness, visual disturbance weakness, headache and confusion. Where a participant experiences such symptoms, the participant is instructed to stop the training immediately, take a rest and eat immediately. To prevent hypoglycaemia during exercise sessions at home, participants were also advised on recommended strategies such as not exercising beyond the recommended intensity and time limits (Fahey et al., 2012), performing resistance exercise before aerobics (Colberg et al., 2016) and injecting insulin at least 60 min prior to exercise (for those using insulin) (Koivisto & Felig, 1978). During the weekly exercise sessions at the physiotherapy department, the PT utilised the glucose management strategy recommended by Riddell et al. (2017). Guided by the strategy, if a participant's starting glycaemia is less than 90 mg/dL, they will be instructed to take 10–20 g glucose and delay exercise until glycaemia is greater than 90 mg/dL. If a participant's glucose is between 90 and 124 mg/dL, they will be instructed to take 10 g of glucose. Participants were not allowed to exercise if their starting glycemia was above 270 mg/dL.

##### Week 2 to week 12

Exercise will be adjusted to 45 min (30 min of walking and 10 min of resistance training plus 5 min of warm‐up and cool‐down) at 75% of maximum heart rate. Participants will continue to engage in three exercise sessions per week, having two sessions self‐administered at home and one supervised session at the physiotherapy department, with no 2 days without exercise.

Resistance training will be graduated from 60% one‐repetition maximum (1RM) and progress to 100% IRM based on the assessment by the PT. The one‐repetition maximum measure refers to how much weight the participant can lift in one repetition. Participants will perform a single set of resistance exercises with 8–12 repetitions, with a between‐set resting interval of 90–120 s.

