### Data collection procedure

2.11

Data relating to demographics, eligibility screening, PA levels and QoL will be collected using online questionnaires. A nurse or research team member who is independent of the participant's care team will provide the participant with a quiet place at the NDMRC and administer the eligibility screening checklist. Similarly, the nurse will follow the same procedure to administer the baseline demographic data questionnaire and the baseline and week‐12 follow‐up IPAQ—SF and SF‐12V2 questionnaires. If a participant is unable to read and/or write in English, the nurse will administer the questionnaires verbally in the local language. Surveys will be completed electronically via a RedCap survey tool.

Prior to each exercise session at the physiotherapy centre, the PT will measure the IG participants' BP, HR and random blood glucose (RBG) using the hospital's standard procedure.

WC will be taken by measuring the mid‐point between the lower costal margin and iliac crest.

A 5‐mL sample of venous blood will be collected after at least an 8‐h overnight fast. Participants will be advised about the need for the overnight fast in the PICF and will be sent a reminder via text. A senior biomedical scientist will collect blood samples and biochemical tests (TG, HDL and FBG) will be performed using the hospital's standard protocol. Blood sample will be collected into a serum separation tube and analysed using a dry chemistry analyser.

During the participants' weekly visit to the physiotherapy department, the PT will assess exercise participation and safety using a checklist for exercise participation and the participants' exercise diary. Measures of participation will be determined by the percentage of sessions attended and the proportion of participants who complete the prescribed PA: 22 sessions of home‐based aerobic exercises and 14 sessions of facility‐based resistance training. An overall score <50% of attendance will be judged as low participation and above 70% will be graded as high participation. A score between 50% and 70% will be graded as moderate participation. Reasons for non‐participation or withdrawal will be documented.

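### Two exercise rules for weeks 2 to 12 (8–12 repetitions at loads up to 100% of 1RM; the rest-day rule with three sessions a week) cannot be followed as written, and the week-1 heart-rate band needs a linking statement

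*Protocol article*

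**What the plan says.** All references are to the protocol article.

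- **Load and repetitions (2.8.1, Week 2 to week 12).** Resistance load starts at 60% of 1RM and may "progress to 100% IRM based on the assessment by the PT". The next sentence says that 1RM "refers to how much weight the participant can lift in one repetition". The one after it begins "Participants will perform a single set of resistance exercises with" and goes on to give 8–12 repetitions. Section 2.10.8 measures 1RM at baseline only.
- **Spacing (2.8.1, Week 2 to week 12).** There are three sessions a week, two at home and one supervised, "with no 2 days without exercise".
- **Heart rate (2.8.1, Week-1).** "Target HR will be based on the recommended safe range of" 64%–76% of maximum, where maximum is 220 minus age. Later in the same paragraph, "Exercise in week 1 will be limited to 35 min", with a target of 50%–60% of maximum. For weeks 2–12 the target is 75%.
- **How exercise is recorded and scored.** Section 2.10.6 collects type, duration, intensity and frequency. Section 2.11 scores participation by sessions attended and completed, out of 14 facility and 22 home sessions, with cut-offs at 50% and 70%.

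**The concern.** The load and spacing rules each appear to conflict with the sentences around them. If so, a therapist has to settle the upper load and the weekly spacing without guidance, and two therapists could settle them differently.

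Two things are at stake. The first is safety. Section 2.8.1 gives keeping within the recommended intensity and time limits as a precaution against hypoglycaemia at home, and 22 of the 36 sessions are done there. That advice needs an intensity that is stated consistently. The second is the purpose of the study. A feasibility trial meant to inform a larger one should hand over a dose that others can reproduce, and the intensity and frequency data need a single prescription to be judged against.

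**Working it through.** **The plan's own session count.** Week 1 has 3 facility sessions. Weeks 2–12 have 11 × 1 = 11 facility and 11 × 2 = 22 home sessions. Facility total: 3 + 11 = 14. Overall: 14 + 22 = 36. This reproduces the stated figures.

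**Load against repetitions.** No arithmetic is needed. By the protocol's definition, a load of 100% of 1RM is one that can be lifted once. The prescription asks for at least 8 lifts. At the top of the 60%–100% range the two statements cannot both hold. The definition alone does not contradict the lower part of the range.

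**Spacing, read literally (no two consecutive days without exercise).**

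1. A repeating week with three sessions has 7 − 3 = 4 rest days, shared among three gaps. At least one gap must hold two or more rest days. Enumerating all C(7,3) = 35 weekly patterns confirms it: 0 of 35 comply.
2. Varying the days from week to week does not help. The rule stands in the text for weeks 2–12, which is 11 × 7 = 77 days with 11 × 3 = 33 sessions. That leaves 77 − 33 = 44 rest days. With s sessions, at most s + 1 rest days can be placed without two in a row, so 33 sessions allow 34.
3. The smallest s that works satisfies s + (s + 1) ≥ 77, so s ≥ 38. The plan has 33, a shortfall of at least 5.

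**Spacing, read as no more than two consecutive days without exercise.** The three gaps must sum to 4 with none above 2. The ordered possibilities are the arrangements of (2, 2, 0) and of (2, 1, 1), 3 + 3 = 6 in all. Each can start on any of 7 days, and each pattern is counted once per session day: 6 × 7 / 3 = 14. So 14 of 35 patterns comply, matching the enumeration.

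**Heart rate.** Both bands are percentages of the same maximum, and 60% is below 64%, so they do not overlap at any age. For illustration, at age 55 (an assumed age) the maximum is 220 − 55 = 165 beats per minute:

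| Target | Calculation | Beats per minute |
|---|---|---|
| Week 1, 50%–60% | 0.50 × 165 to 0.60 × 165 | 82.5 to 99 |
| Stated range, 64%–76% | 0.64 × 165 to 0.76 × 165 | 105.6 to 125.4 |
| Weeks 2–12, 75% | 0.75 × 165 | 123.8 |

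The target for weeks 2–12 lies inside the stated range. The week-1 band lies wholly below it.

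**The case against.** **On load.** Progression depends on the therapist's assessment, and 1RM is measured only at baseline, so 100% of the baseline value could become submaximal as participants gain strength. That is possible, but the protocol does not say it, and the conflict with its definition remains. What stands is that only the upper end is affected.

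**On spacing.** The phrase may have been meant as no more than two consecutive days, and then three sessions a week fit. That is a fair reading, but it differs from the literal one. The text should say which is meant.

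**On heart rate.** Week 1 is described as limited and the following weeks as adjusted upwards, so each week has one stated target and a graded start is plausible. This largely stands, and it is why the point is a lesser one. What is missing is a statement that the 64%–76% range does not apply in week 1.

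A reader might also infer more than the documents support:

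- *That the programme cannot be scored.* The participation score counts sessions, and the counts reconcile. Load, repetitions, heart rate and spacing do not enter it.
- *That a single set with a between-set rest is contradictory.* Three resistance exercises are listed, so the rest can fall between them. With one set of each, two rests and an assumed 3–6 seconds per repetition, the work takes from (3 × 8 × 3 + 2 × 90)/60 = 4.2 to (3 × 12 × 6 + 2 × 120)/60 = 7.6 minutes, inside the 10-minute block.
- *That week 1 breaks the weekly time goal.* Week 1 gives 3 × 35 = 105 minutes against a goal of at least 120. But week 1 is expressly limited, and later weeks give 3 × 45 = 135.
- *That the glucose checks conflict.* Fasting glucose belongs to the assessment at the start of week 1. Section 2.11 measures "BP, HR and random blood glucose (RBG") before each physiotherapy session. These are different times.

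**Conclusion.** The concern holds for two rules and, as a point of clarification, for a third statement.

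1. Loads up to 100% of 1RM with 8–12 repetitions contradict the protocol's own definition of 1RM. This concerns the top of the range and rests on that definition alone.
2. The spacing rule, read literally, is impossible with three sessions a week in weeks 2–12. It is feasible only under a different reading of the phrase.
3. The two heart-rate bands in the Week-1 text do not overlap, and no sentence links them. A graded start is the likely intention.

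A reader might conclude that the whole programme is undeliverable. It is not: only the upper load and the literal spacing rule are. Nothing here touches randomisation, the outcome definitions, the attendance-based participation score or the between-group analysis. The consequence is for how the intervention is described, how safely and uniformly it is delivered, and whether fidelity can be judged. It is worth correcting before the first session because most sessions are unsupervised and the correction is cheap.

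**What to change.** Before the first session, the investigators and the physical therapy lead should:

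- reconcile the load statement with the repetition count and the definition of 1RM in section 2.8.1 (Week 2 to week 12);
- reword the spacing rule so that it has one meaning and is compatible with the number of weekly sessions;
- state in the Week-1 text how the 50%–60% band relates to the 64%–76% range;
- align the therapist's checklist and the exercise diary with the reconciled text, so that the intensity and frequency data under section 2.10.6 are judged against one prescription.

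The values are a clinical decision for them, and none is proposed here. The cost is a clarifying amendment to the intervention section and matching edits to the therapist's materials. No extra visits or participants are needed, and the analysis does not change.

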#### Control group

2.8.2

The CG will maintain their usual diabetes care, including glucose‐lowering medication, dietary management, footcare and regular outpatient care. They will be encouraged to continue their usual PA but will not be referred to a PA programme. They will not be contacted during the RCT and will attend all medical appointments as organised by hospital staff.

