#### Primary measures

2.9.1

The primary outcome is a change in MetS markers (BP, TG, WC, FBG and HDL) in Ghanaian adults with T2DM who participate in a 12‐week PA programme, compared to those who receive usual diabetes care.

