#### Physical, clinical and biochemical data

2.10.5

Blood pressure and heart rate will be taken during the baseline visit for all participants and during each exercise session at the physiotherapy department for participants in the IG group. Blood pressure will also be measured at the 12‐week follow‐up. WC will be measured at baseline and at the 12‐week follow‐up. A blood sample will be collected at baseline and at the 12‐week follow‐up to measure Fasting Blood Glucose (FBG), high‐density lipoprotein (HDL) and triglycerides (TG).

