### Sample size

2.12

Feasibility studies are designed to obtain preliminary data (Eldridge et al., 2016). Billingham et al. (2013) examined sample size for feasibility RCTs and found a median sample size of 72 (36 per arm). They concluded that while it is important to justify sample size in feasibility RCTs, calculating sample size may not be appropriate. Thus, this proposed study will aim for a sample of 72 participants. To account for attrition, a 20% adjustment will be added. Therefore, the target sample size for this feasibility study will be 90 participants: 45 in each group.

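### The unqualified no-contact rule for controls conflicts with the fasting text reminder before the week-12 blood draw; applied literally, it could make the measurement conditions for glucose and triglycerides differ by arm

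*Protocol article*

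**What the plan says.** Section 2.8.2 (Control group) describes usual diabetes care, says that controls will not be referred to an activity programme, and closes with: "They will not be contacted during the RCT and will attend all medical appointments as organised by hospital staff". It states no exception for outcome visits or reminders.

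Section 2.11 (Data collection procedure) requires blood to be drawn after an overnight fast of at least 8 hours and says how the fast is to be secured: "Participants will be advised about the need for the overnight fast in the PICF and will be sent a reminder via text". This is worded for participants in general, not for one arm or one visit.

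Section 2.10.5 places the blood sample for fasting glucose, HDL and triglycerides at baseline and at the 12-week follow-up. Section 2.9.1 counts fasting glucose and triglycerides among the five primary markers, and section 2.13 adds the components into a metabolic syndrome Z-score.

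For the intervention group, section 2.8.1 describes weeks 2 to 12 as "having two sessions self‐administered at home and one supervised session at the physiotherapy department". All three sessions in week 1 are also at the hospital.

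**The concern.** A site that obeys section 2.8.2 to the letter cannot text a control before the week-12 draw. A site that obeys section 2.11 must do so. Different staff could resolve the conflict in different ways.

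The literal no-contact reading would tie the preparation for a fasting measurement to the arm. Both glucose and triglycerides tend to be higher after food. If fewer controls arrived fasted, control values at week 12 would be raised and the programme would appear to improve two primary markers and the summed score, whatever the exercise achieved. Neither the t-test nor the Mann-Whitney test named in section 2.13 could separate that error from a treatment effect. Blinding the outcome assessors (section 2.7) would not help either, because whether the participant has eaten is settled before the assessor sees them. The trial is meant to supply preliminary evidence of effect for a larger trial, so an error in one direction would carry forward into that design.

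**Working it through.** No figure in the plan expresses this point, so the check is a comparison of the sections.

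1. **Baseline draw.** Section 2.5.1 places randomisation at the baseline visit. A reminder before that visit goes to people not yet allocated, so the no-contact rule has nothing to act on and no difference between arms is expected.

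2. **Week-12 draw.** A reminder for this draw has to be sent after allocation and before the last visit, that is, during the trial. The unqualified rule in section 2.8.2 then forbids it for controls, while section 2.11 promises it to participants.

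3. **What controls keep under the literal reading.** They keep the fasting advice in the information form. That form is given at recruitment (section 2.5), and written consent is taken at the screening visit (section 2.6), so the advice is about 12 weeks old or more at the final draw. For those who cannot read, it was read aloud.

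4. **What the intervention group has.** It has the form, the text and regular attendance at the same hospital. From the weekly schedule, supervised attendances are 3 in week 1 plus 11 × 1 in weeks 2 to 12 = 14, which reproduces the 14 facility sessions in section 2.8.1. Controls have no trial attendance between baseline and week 12.

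5. **Does the rest of the sentence in section 2.8.2 settle it?** It says that hospital staff organise medical appointments. It follows a description of routine outpatient care and does not mention the research visit or the fasting sample. It may offer a route for scheduling, but it does not supply the reminder.

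6. **Direction of any error.** Let p_C and p_I be the shares not fasted at week 12 in the control and intervention groups, and let d be the mean rise in a marker when not fasted, taken as equal in both arms. The expected error in the difference, intervention minus control, is (p_I − p_C) × d. With d > 0 and p_C > p_I it is negative, which looks like benefit. With p_C = p_I it is zero.

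7. **Size.** The documents give none of p_C, p_I and d, and no standard deviation for either marker. The size therefore cannot be derived from them.

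**The case against.** The strongest reply is that section 2.8.2 sits under Interventions and describes the comparator. Its natural sense may be no intervention-type contact between baseline and follow-up. A total ban on contact would sit badly with the 12-week measurements that the article schedules without restriction to one arm. Section 2.11 is the specific rule for data collection and covers both arms, and section 2.4 excludes anyone without a mobile phone, which fits texting everyone. This is a fair account of what the authors may have intended. It does not change the text, which states no such limit and leaves a site to guess.

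A reader might infer several stronger things that the documents do not support:

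- *That the samples will be taken under different conditions.* No section sets a different fast, reminder or visit schedule for controls. The difference arises only if the no-contact rule is applied literally.
- *That the fast rests on the text alone.* The information form gives the same advice to both arms.
- *That the physical therapist reminds the intervention group to fast.* The listed duties are supervision, clinical checks, participation and safety. Weekly attendance gives an opportunity, not a stated reminder.
- *That controls are not called to week 12.* The visit schedule is in Figure 1, which is not available here.
- *That the single attrition allowance is wrong.* Section 2.12 says "To account for attrition, a 20% adjustment will be added", and 72 / 0.80 = 90 reproduces the target. One overall figure is ordinary and is not an error.
- *That the absence of a stated fasting check at the draw is a fault.* A condensed article may leave this to the full protocol or laboratory procedure.

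**Conclusion.** The conflict is real but narrow. Sections 2.8.2 and 2.11 cannot both be followed for a control's week-12 fasting draw, and they need to be reconciled. A bias in favour of the programme on fasting glucose, triglycerides and the metabolic syndrome score is possible, not established. It requires three things: that the no-contact rule is applied as written, that fewer controls than intervention participants then arrive fasted, and that non-fasted values are higher. Unequal attendance at week 12 is a possible consequence on the same footing. Any figure in mg/dL would rest wholly on invented inputs, so none is offered. The correction is still worth making, because the possible error runs in one direction, touches two of the five primary markers, and costs almost nothing to prevent.

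**What to change.** Amend the last sentence of section 2.8.2 to say that controls receive no intervention contact during the trial, but get the same week-12 appointment notice and fasting reminder text, at the same times, as the intervention group. Section 2.11 could add that the reminder goes to both arms before both draws.

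Optionally, record the time of last food at each draw in both arms, so that compliance with the 8-hour fast already required can be checked and compared.

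The cost is a change of wording, one or two text messages per control and, if the option is taken, one field on the sample form. Every participant must already have access to a mobile phone. The notice and reminder are not part of the activity programme, so the contrast between the arms is preserved.
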